### Trial management

An independent data monitoring committee will be established, with terms of reference jointly defined between trial investigators and the independent committee members prior to study commencement. A multidisciplinary adverse events committee blinded to treatment allocation will review the cause of death for all maternal and infant deaths. These data will be made available to the independent data monitoring committee. In addition, the committee will conduct an interim analysis midway through the trial after the inclusion of 189 women. They will be unaware of treatment allocation when they judge data on effectiveness and safety and will compare these against the stopping rules outlined in the terms of reference. All study investigators have agreed to meet on a monthly basis to monitor trial progress and procedure. A respiratory physician who specialises in asthma management will provide a quality assurance review of the asthma management clinic every 6 months at both sites.

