### Randomization

After the baseline assessment of asthma at 18 weeks gestation, women will be randomised to receive either standard care or nurse-led asthma management during pregnancy by contacting the central telephone randomization service at the University of Adelaide. The telephone randomization service will use a randomization schedule with balanced variable blocks, prepared by an investigator not involved with recruitment or clinical care. Stratification will be undertaken according to treatment site, parity and asthma severity. During the randomization call, eligibility will be checked and information collected to enable stratification and to assist in follow-up.

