### Data collection

All women will receive a baseline assessment of their asthma as previously described. Data will be collected on participants receiving standard care by a trained research midwife and those receiving the intervention by the respiratory nurse at 24, 30 and 36 weeks gestation. This will be undertaken using a structured data collection tool. At each time point asthma control will be assessed using the ACQ and spirometry. Further data will be collected using a cold and flu questionnaire to determine the impact of illness on current asthma control. A current pregnancy related history will be collected by research midwife interview for any unscheduled doctor visits due to asthma, an increased use of inhaled glucocorticoid, any visits to the Emergency department and any hospital admissions related to asthma, occurring since the previous visit. These data will be used to determine the number and timing of any asthma exacerbations occurring during the study. Data on asthma medication use will be utilized to calculate a cumulative ICS dose for each trimester. In addition, women will be asked to complete a questionnaire relating to smoking (direct and passive), and asthma related quality of life. Furthermore, data will be collected on the level of care received for asthma management from a GP, obstetrician or respiratory specialist (i.e. type and number of visits). Women receiving care through the Antental Asthma Management Service will have additional data collected on psychological variables as outlined in the section on data collection at trial entry (i.e. Perceived Control of Asthma Questionnaire [33]). Medicare Benefits Scheme (MBS) and Pharmaceutical Benefits Scheme (PBS) data relating to medical care and medication use throughout pregnancy will be accessed by participant consent. For all women, data on pregnancy complications, labour, delivery and birth outcomes will be abstracted from delivery case notes.

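### The data monitoring committee is masked to allocation while it judges effectiveness and safety at the interim, with no stated route to unmask, so it cannot tell benefit from harm

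*Protocol article*

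**What the plan says.** The Trial management section of the protocol article sets up two bodies.

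- **Data monitoring committee.** "An independent data monitoring committee will be established, with terms of reference jointly defined between trial investigators and the independent committee members". Its interim task is that "the committee will conduct an interim analysis midway through the trial after the inclusion of 189 women". On masking, the section says: "They will be unaware of treatment allocation when they judge data on effectiveness and safety and will compare these against the stopping rules".
- **Adverse events committee.** "A multidisciplinary adverse events committee blinded to treatment allocation will review the cause of death for all maternal and infant deaths". Its findings go to the data monitoring committee.

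The section does not say whether the interim report is pooled or split into coded arms. It describes no unmasking step and gives neither the form nor the direction of the stopping rules. Those rules sit in the terms of reference, which are not shown.

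The arms differ in kind. The Randomization section says that "women will be randomised to receive either standard care or nurse-led asthma management during pregnancy". The Standard care group section describes existing practice, and the Intervention group section adds nurse-led visits at 18, 24, 30 and 36 weeks.

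**The concern.** This is a stated rule about what the committee may know, not a detail left out of a condensed article. Terms of reference can add boundaries and report formats, but giving members the allocation while they judge the data would contradict the sentence as printed.

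The two arms are not interchangeable. One is care that women would receive anyway; the other is an added service. Evidence that the service does harm and evidence that it helps usually call for different thresholds and lead to different recommendations. Members who do not know which arm is which also cannot weigh one outcome against another. Fewer exacerbations with more neonatal admissions in arm A means one thing if A is the service and the opposite if A is standard care.

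At stake is the trial's one stated comparative look at safety and effectiveness, in pregnant women and their infants.

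**Working it through.** **Inputs from the protocol article.** Total 378 women; 45% against 25% with an exacerbation; two-sided testing at 0.05 (Sample size, Statistical analysis). Interim after 189 women (Trial management).

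**The plan's own figure.** 189/378 = 0.50, so the interim is midway, as stated. Per arm this is 189/2 = 94.5; 94 is used below, with outcomes assumed complete.

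**Reading 1: pooled report.** If the service lowers the rate from 45% to 25%, the pooled rate is (45 + 25)/2 = 35%. If the service instead has 45% and standard care 25%, it is again 35%. Pooled data carry no information on a difference between arms.

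**Reading 2: coded arms A and B.** Let z = (p_C − p_T)/√(2p̄(1−p̄)/n), positive when the service does better. Coding the arms at random multiplies z by +1 or −1, so the committee sees |z| but not its sign. The protocol gives no boundary, so 3 and 1.96 are assumptions for illustration. Each setting had 400,000 simulated interims.

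| Truth | \|z\| > 3 | 1.96 < \|z\| ≤ 3 |
|---|---|---|
| No difference (45% in both) | 0.25% | 4.5% |
| Benefit (standard care 45%, service 25%) | 45.7% | 37.2% |
| Harm (standard care 25%, service 45%) | 45.8% | 37.2% |

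Hand check for the benefit row:
- Expected z = 0.20/√(2 × 0.35 × 0.65/94) = 0.20/0.0696 = 2.87.
- Standard deviation of z = √((0.45 × 0.55 + 0.25 × 0.75)/94)/0.0696 = 0.0680/0.0696 = 0.98.
- P(z > 3) = 1 − Φ(0.13) ≈ 0.45.
- P(1.96 < z ≤ 3) = Φ(0.13) − Φ(−0.94) ≈ 0.38.

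Both agree with the simulation to within about one percentage point.

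**What this shows.**
- *Symmetric rule, stop if |z| > 3.* Masked and unmasked crossing decisions agreed in 100% of simulations, so masking does not stop such a rule from being applied. The benefit and harm rows are the same to within simulation error, so a committee that sees a crossing cannot say which has occurred.
- *Directional rule, stop for harm at z < −1.96 and for benefit only at z > 3.* When 1.96 < |z| ≤ 3, the rule says stop if the service is worse and continue if it is better. At a true 20-point difference in either direction, about 37% of interims fall there, and the rule cannot be applied without arm identity.

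**The case against.** The strongest reply is that the deciding facts are in terms of reference that we cannot see. The sentence masks members only while they judge the data. That fits coded reports and a symmetric boundary, with the code opened once the boundary is crossed. Much of this stands. A reader might infer that the stopping rules cannot validly be applied at all, and the documents do not support that. It would be true only if the data were pooled or the rules directional, and the article says neither.

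A reader might also gauge the problem by the chance of a nominal p<0.05 at the interim under the planned effect. That is not a probability of a wrong stopping decision, and nothing in the article makes p<0.05 a boundary.

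Nor is it unclear which committee is meant. The data monitoring committee is named immediately before the interim is described, and that is the natural reading.

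Masking also has a purpose: it guards members against judging by their expectations of the service. The protection may be thin, because "Women receiving care through the Antental Asthma Management Service will have additional data collected on psychological variables", and perceived control, adherence and asthma knowledge are secondary outcomes. A coded report that included these data would show which arm is the service. A report limited to exacerbations and safety would not, so this is a side point.

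What the reply does not meet is that crossing a boundary is only a trigger. Deciding what to recommend needs the direction of the difference, and the article states no way to obtain it.

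**Conclusion.** The concern holds in a limited form. A data monitoring committee held to this sentence cannot compare the arms at all if the report is pooled. If the arms are coded, it can apply a symmetric boundary but cannot tell benefit from harm, apply a directional rule, or weigh effectiveness against safety.

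The 37% is the size of the problem under one assumed directional rule, 94 women per arm with complete outcomes, and a true 20-point difference. It is an illustration, not an estimate of how this trial's own rules would behave. If the terms of reference provide coded arms, a symmetric boundary and unmasking on request, the practical gap is small, and what remains is a protocol sentence that does not say so. The final analysis is not affected. The sentence is worth changing because the weakness lies in safety monitoring and the remedy is cheap.

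**What to change.** Amend the sentence in Trial management, and the terms of reference to match, so that:

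1. The data monitoring committee receives interim effectiveness and safety data by arm in closed session, either identified or coded A/B.
2. If coded, the code is available to the committee on request. It is always opened before any recommendation to stop or continue once a boundary has been crossed or a safety concern has arisen.
3. Investigators and site staff stay unaware of the interim comparisons.
4. The adverse events committee stays blinded for its review of causes of death. That is a separate task in which blinding has a clear use.

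The cost is one protocol sentence and a matching clause in the terms of reference, with no added data or participants. The small downside is that committee members may know the arm; confidentiality of the closed session limits this, and the coded option limits it further.

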## Discussion

The clinical and cost effectiveness of an Antenatal Asthma Management Service has not been rigorously evaluated to date through a randomized controlled trial. Asthma is the most prevalent chronic medical condition to affect human pregnancy and is expected to increase in coming years, representing a significant burden for the healthcare system. This associated burden lies in coping with the increasing demands of caring for pregnant women with asthma and in dealing with its associated adverse effects on perinatal health outcomes.

The need for, and potential of, an individualized review of asthma management during pregnancy has been well demonstrated in previous research undertaken through this research group [17]. Given finite resources, however, it is unlikely that existing models of practice could cope with the increased requirements of providing an asthma management service as outlined in this protocol, highlighting the importance of this clinical and cost effectiveness analysis.

The provision of an Antenatal Asthma Management Service conducted by a respiratory nurse provides an alternative approach for the introduction of education for asthma self-management skills and the provision of an asthma action plan. Working in close consultation with each woman’s primary health care provider (i.e. GP) and hospital-based midwives and specialist physicians, the respiratory nurse is able to play a key role in guiding optimized asthma management and empowering pregnant women to manage their asthma more effectively. The introduction of this intervention has a significant potential to improve current clinical care of pregnant women with asthma and lead to a significant reduction in the incidence and severity of asthma exacerbations, improve asthma control and related quality of life and decrease the negative impact of asthma on a range of Perinatal health outcomes. These improvements in health outcomes are of major benefit to the health care system, as there are significant costs associated with managing exacerbations (i.e. unplanned medical and emergency department visits, hospitalizations), maternal complications (i.e. pre-eclampsia) and neonatal complications (i.e. low birth weight) associated with maternal asthma. In addition to immediate costs, many of these outcomes are associated with long-term morbidity for the child and adult, representing a substantial ongoing cost and health burden to society for the entire life span of these individuals [43].

The data generated from this study will provide strong evidence in support of new policies for the care of pregnant asthmatic women and models of health service delivery. A significant benefit of this proposal lies in the fact that the intervention can be introduced in any setting where pregnant women are cared for, which include hospitals, GP offices and regional health services. Furthermore, an established relationship between the research group and asthma organizations (i.e. Asthma Australia) will ensure the effective dissemination of the results and recommendations of this study to clinical practice.

## Abbreviations

ACQ: Asthma control questionnaire; FEV1: Forced expiratory volume in one second; FENO: Exhaled fraction of nitric oxide; FMC: Flinders medical centre; GP: General practitioner; ICS: Inhaled corticosteroid; IUGR: Intrauterine growth restriction; LMH: Lyell MCewin hospital; NICU: Neonatal intensive care unit; OR: Odds ratio; QALY: Quality adjusted life year; RR: Relative risk.
